**FIGURE 3 F3:**
[figure not shown]
Flow chart of the study.

We will cluster randomize at the preschool level, since we regard delivery of the intervention on the preschool level the only practical approach. A third party ([name], Norwegian School of Sport Sciences) will randomize ≈ 60 preschools to the intervention group (≈ 30 preschools) or the standard of care control group (≈ 30 preschools). Randomization will be done separately in the two study waves after completing recruitment and before initiating baseline data collection using a random number generator (Stata/SE 15.1, StataCorp LLC, College Station, TX, United States). We will use block randomization (randomly chosen block sizes of 4 and 6) and a 1:1 ratio for the two intervention arms. Blinding of participants and preschools is not possible due to the nature of the experiment. To limit potential biases, the fewest possible assessors involved in project management, data collection, and statistical analysis will have knowledge about the group assignment and the study hypotheses.

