##### Socioemotional health, self-regulation, executive function, and learning

We will adapt several validated tests to examine different aspects of socioemotional health, self-regulation, executive functions, and learning. Yet, there exists little agreement on the optimal measures and their configuration for capturing important aspects of early cognitive development (Garon et al., 2008; Howard and Melhuish, 2017).

To assess **socioemotional health,** we will ask the teachers to fill out the Strengths and Difficulties Questionnaire (SDQ) for each child. The SDQ is a brief measure of psychosocial strengths and problems in 3- to 16-years-old children. The SDQ asks about 25 attributes (10 positive, 14 negative, and 1 neutral) divided between five subscales of five items each: (*1) Emotional Symptoms Scale; (2) Conduct Problems Scale; (3) Hyperactivity Scale; (4) Peer Problems Scale;* and (*5) Prosocial Scale*. All but the last scale are also summed to give a total difficulties score. SDQ uses a 3-point Likert scale to indicate the extent to which each attribute applies to a child (“not true,” “somewhat true,” or “certainly true”) (Goodman, 1997, 2001). The construct validity of the SDQ has been demonstrated in several studies (Goodman, 2001; Stone et al., 2010; Mieloo et al., 2012), and the reliability and validity of the SDQ has been shown to be satisfactory (Goodman, 2001; Stone et al., 2010). The teacher version of the SDQ has shown both higher internal consistency and test-retest reliability compared to the parent version for preschool and schoolchildren (Stone et al., 2010; Mieloo et al., 2012).

**Self-regulation** will be assessed both by teacher-report and a structured observation (direct measure) of a child’s performance. Teachers will be asked to fill out the 33-item Child Self-regulation and Behavior Questionnaire form from the Early Years Toolbox (EYT) (Howard and Melhuish, 2017). The Child Self-regulation and Behavior Questionnaire generates subscales on cognitive, behavioral, and emotional self-regulation, in addition to sociability, prosocial behavior, externalizing and internalizing problems, which overlaps with the SDQ. Each item asks the teacher to evaluate the frequency of target behaviors of each child on a scale from 1 (not true) to 5 (certainly true). The subscales of the questionnaire have been shown to be reliable in preschoolers (Howard and Melhuish, 2017).

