### Analysis Plan

#### The Child Level

##### Primary aim

The main analyses of child-level effects will employ an intention-to-treat principle, thus including all subjects and preschools originally allocated to the respective groups, to test the study’s effectiveness (Polit and Gillespie, 2010). However, as shown for the school setting (Donnelly et al., 2009), there are strong arguments for including per-protocol analyses for the examination of efficacy. Therefore, we will perform secondary analyses limited to preschools that exhibit acceptable intervention adherence. Missing data will be sought, minimized, detailed, and handled in line with suggested guidelines (Little et al., 2012). Attrition analyses will be performed to investigate whether missing data are related to child characteristics. Missing data will be handled by the use of linear mixed models (LMMs) and structural equation modeling (SEM) (Enders, 2011; Little, 2013).

Intervention effects will be evaluated by testing for time^∗^group interactions for all outcomes. The per-protocol analysis will be adjusted for differences between the groups, as appropriate. LMM and multilevel SEM for mediation analyses (SEM) (Little, 2013) will be used to account for clustering of observations on the preschool level in all analyses. A two-sided *p* ≤ 0.05 is considered statistically significant; however, both ESs and patterns of effects across variables will be considered of greater importance than *p*-values when drawing study conclusions. Consistent with this approach, *p*-values will not be adjusted for multiple testing. Main analyses will be performed using IBM SPSS v. 25 (IBM SPSS Statistics for Windows, Armonk, NY: IBM Corp., United States) or later versions and MPLUS v. 8 or later versions (Muthén and Muthén, Los Angeles, United States). Reporting will be done in accordance with the CONSORT statement (Campbell et al., 2012).

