We regard children’s cognition as the main study outcome. However, we include several aspects of cognition in the present study (socioemotional health, self-regulation, executive functions, and learning), of which designating one focused outcome *a priori* is challenging and inappropriate based on the current level of evidence of effects of PA in young children (Carson et al., 2016; Alvarez-Bueno et al., 2017a, b; Singh et al., 2019). These constructs will be analyzed as separate variables, to retain their unique information, as well as latent variables, to remove measurement error and establish broader constructs, and thus obtain both specific as well as broader knowledge about the effect of PA on cognitive outcomes. Children’s PA, physical fitness, motor competence, adiposity, and staff PA are regarded secondary outcomes.

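### Unblinded teacher ratings stand level with directly assessed tests as main cognition outcomes, so an arm-wide change in how teachers rate could be read as an effect on the child

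*Protocol article*

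**What the plan says.** **Standing of the outcomes.** The Primary aim section of the Analysis Plan states: "We regard children’s cognition as the main study outcome". It counts socioemotional health, self-regulation, executive functions and learning as aspects of cognition and declines to choose one of them in advance. On analysis it says: "These constructs will be analyzed as separate variables, to retain their unique information, as well as latent variables, to remove measurement error".

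**Who measures what.** The section on socioemotional health, self-regulation, executive function and learning gives:
- Socioemotional health: "we will ask the teachers to fill out the Strengths and Difficulties Questionnaire (SDQ) for each child". There are five subscales and a total difficulties score, and no second source.
- Self-regulation: "will be assessed both by teacher-report and a structured observation (direct measure) of a child’s performance". For the first part, "Teachers will be asked to fill out the 33-item Child Self-regulation and Behavior Questionnaire form", which yields seven subscales. The second part is the Head-Toes-Knees-Shoulders task.
- Executive functions: three iPad tasks. Learning: vocabulary and numbers tasks. All five are assessed directly.

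**Who knows the arm.** Protocol and Randomization states: "Blinding of participants and preschools is not possible due to the nature of the experiment". The safeguard given there limits knowledge of allocation and hypotheses among project assessors and does not mention teachers as raters. Staff deliver the intervention (Modes of delivery). The director and at least one teacher per classroom are asked to take the course (Table 2).

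**How conclusions are drawn.** Effects are time-by-group interactions, with no multiplicity adjustment, and "both ESs and patterns of effects across variables will be considered of greater importance than" p-values. Self-regulation and socioemotional characteristics are also named as mediators (Secondary analyses of intervention effects).

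**The concern.** A teacher rating records the child and the teacher's standard together. Intervention teachers work for months in a programme meant to improve child development, and the 7-month follow-up falls at the end of the course. Control teachers continue standard care. Expectation could make intervention teachers more generous. Better knowledge of child development could make them stricter. Either way, the arms could differ with no difference in the children, or a real difference could be hidden.

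Three features of the plan would pass such a shift into the main conclusion:

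1. **Interaction test.** A shift at follow-up in one arm is a time-by-group effect. Modelling preschool clustering corrects the variance but leaves a systematic difference between arms in place.
2. **Latent variables.** A factor removes error that is independent between items. A shift common to the items a teacher rates is shared variance, so the factor keeps it.
3. **Reading patterns.** The self-regulation questionnaire overlaps with the SDQ, as the article notes. One changed impression can therefore appear as several agreeing results.

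The same shift could carry into mediation results that use the ratings.

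**Working it through.** **1. Share of teacher-rated scores**

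Inputs come from the section on socioemotional health, self-regulation, executive function and learning.
- Teacher-rated: SDQ 5 subscales + questionnaire 7 subscales = 12.
- Direct: Head-Toes-Knees-Shoulders 1 + executive function 3 + learning 2 = 6.

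| Way of counting | Teacher-rated | Share |
|---|---|---|
| Subscale scores | 12 of 18 | 67% |
| Same, adding the SDQ total | 13 of 19 | 68% |
| SDQ 5 + the 3 self-regulation subscales only | 8 of 14 | 57% |
| Instruments | 2 of 8 | 25% |
| Constructs | 1 of 4 wholly, 1 partly | |

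**2. The plan's own precision**

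Inputs come from the Participants section: median 18 children per preschool, 30% attrition, coefficient of variation 0.65, ICC 0.05 to 0.10, 30 preschools per arm, correlation r = 0.6 to 0.7, 80% power, two-sided 0.05.

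Design effect DE = 1 + ((1 + CV²)m − 1) × ICC, with m = 18 × 0.7 = 12.6:
- ICC 0.05: 1 + (1.4225 × 12.6 − 1) × 0.05 = 1.846
- ICC 0.10: 1 + (1.4225 × 12.6 − 1) × 0.10 = 2.692

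These match the stated 1.85 to 2.69.

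Detectable effect for a change score = √(2 × (1.96 + 0.84)² × DE × 2(1 − r) / n), with n = 30 × 12.6 = 378 per arm and r = 0.6. This gives 0.248 and 0.299, matching the stated 0.25 to 0.30.

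**3. Chance of p ≤ 0.05 with no child effect**

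The documents give no rater shift, so b is an assumption, shown over a range. For a shift of b SD in the intervention arm only:

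P = 1 − Φ(1.96 − b/SE) + Φ(−1.96 − b/SE)

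*Route A.* Take SE from the stated detectable effects, SE = effect / 2.80.

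| Stated detectable effect | SE | b = 0.10 | b = 0.20 |
|---|---|---|---|
| 0.20 (7 months) | 0.071 | 29% | 80% |
| 0.25 (18 months) | 0.089 | 20% | 61% |
| 0.30 (18 months) | 0.107 | 15% | 46% |

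*Route B.* Take SE = √(2 × DE × f / 400), with f = 2(1 − r) for change scores or 1 − r² for baseline adjustment.
- Smallest SE: DE 1.85, r 0.7, f = 0.51, SE = 0.069.
- Largest SE: DE 2.69, r 0.6, f = 0.80, SE = 0.104.

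| Shift b | Chance of p ≤ 0.05 per scale |
|---|---|
| 0 | 5% |
| 0.10 SD | 16 to 31% |
| 0.20 SD | 49 to 83% |
| 0.30 SD | 82 to 99% |

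Together the two routes give 15 to 31% at 0.10 SD and 46 to 83% at 0.20 SD.

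**The case against.** **Most of the main outcomes are teacher-rated.** A reader might infer this. It holds only when subscales are counted. By instrument and by construct it fails. The sentence on patterns also follows tests for all outcomes: adding six accelerometer measures, three fitness tests, three motor domains and two adiposity measures makes the share 13 of 33 (39%). This objection stands.

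**The raters are the trained course participants.** This is probable, but the article does not say so. It says only that teachers complete the forms. Any rater on the staff would still be unblinded in a preschool where the whole staff is involved.

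**The size is assumed.** True, and the direction is unknown as well. The ICCs in the Participants section come from physical activity, motor competence and academic performance. Variance shared within a rater could raise the ICC and lower the probabilities above. They are illustrations, not estimates.

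**Individual teachers' quirks are absorbed by the mixed model.** Largely so for shifts that vary between preschools. The point concerns only a shift in the arm mean, which that model does not remove.

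**The plan already gives some protection.** Constructs are also analysed as separate variables, and self-regulation has a direct test, so disagreement would be visible. The article does not say that the two sources will be mixed in one factor. However, no rule says how disagreement would be read, and socioemotional health has no direct test. The article justifies the teacher SDQ by better reliability than the parent version, which does not address a shift in one arm.

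**Socioemotional health should be made secondary.** The documents do not compel this. It would change the outcome hierarchy of a registered trial, and labelling the source with a cautious reading deals with the problem.

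**Conclusion.** The concern holds in this limited form. All socioemotional-health scores and the questionnaire part of self-regulation are ratings by unblinded teachers, and the Primary aim section treats them as equal to the direct tests. An arm-wide rating shift at follow-up would be reported as an intervention effect. A modest assumed shift of 0.10 SD raises the false-positive chance per scale from 5% to 15 to 31%, and 0.20 SD raises it to 46 to 83%. These figures assume no true effect, a shift in one arm only, and the precision that the protocol plans for.

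The point concerns follow-up ratings and does not depend on when baseline is collected. Protocol and Randomization contradicts itself on that, placing baseline both before and after randomization. If it comes after, baseline ratings could also be made with allocation known.

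The documents do not show that a shift will occur or in which direction. The executive function, learning and Head-Toes-Knees-Shoulders results do not depend on teacher ratings.

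**What to change.** In Primary aim and Secondary analyses of intervention effects:

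1. Analyse and report the SDQ and the teacher self-regulation questionnaire as a separate group, labelled as ratings by unblinded teachers. Keep them apart from the direct tests: Head-Toes-Knees-Shoulders, the three executive function tasks, vocabulary and numbers.
2. Do not combine the two sources in one latent variable. Describe any factor built on teacher items alone as teacher-reported.
3. Run the mediation through self-regulation with the direct test, and use the questionnaire version as a sensitivity analysis.
4. State that a pattern seen only in teacher ratings will not by itself be read as an effect on the child.

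This needs no new data, and socioemotional health can remain a main outcome. The cost is that any conclusion on socioemotional health, which has only a teacher rating, becomes more cautious.

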#### The Preschool Level

The aim of the process evaluation is to explore how staff in the intervention preschools respond to their enrollment in professional development and how the proposed new way of working with PA gains traction in different contexts. We aim to explore the processes and mechanisms through which professional development, alongside working in partnership with researchers, influence the way staff organize and integrate PA practices into their daily operations. We will also explore *if* and *why* intervention effects may vary between preschools. The flexible intervention approach, and thus the variation in activities (likely) taking place in each preschool, means that an examination of typically quantitative measures of implementation such as fidelity, dosage, and adherence might be less feasible and informative. Hence, the process evaluation includes complementary qualitative and quantitative measures of implementation to support the evaluation of the intervention’s ability to change practice, as also recommended previously (Bonell et al., 2012; Pesce et al., 2016).

##### Staff experiences and perspectives

To provide in-depth accounts of how the intervention preschools develop and implement PA into their daily operations, all intervention preschools will be invited to participate in a qualitative study. Data will be collected using semi-structured in-depth interviews and focus groups. More specifically, in-depth interviews will be used to explore the views of the teachers enrolled in the professional development regarding the relevance and delivery of it. For example, teachers will be asked about how they make sense and engage with the central components of the ACTNOW professional development program. Further, in-depth interviews will be used to explore the directors’ and teachers’ roles in leading the development work taking place in each preschool. For example, questions will be asked to explore how they perceive their role in driving the intervention and the preschool’s PA practices forward as well as what actions and procedures they plan to undertake to lead the process. Focus groups will be used to explore how *all* staff perceive the role of environmental mechanisms in shaping the integration of PA practices into their daily operations. More specifically, staff will be asked about their collective understanding of the intervention and its core components. They will also be asked about their willingness to engage in the developmental work taking place in each preschool and what mechanisms that either promote or hinder engagement and participation.

The literature on implementation, in particular the Normalization Process Theory (May and Finch, 2009), and the characteristics of the ACTNOW project and logic model, have been used to inform the interview guides. The interview guides will be revised and adjusted during data collection to allow for the inclusion of case-specific questions and more detailed exploration of emerging themes. As recommended by Durlak (2016), data will be collected at several time points to allow for an examination of the process of implementation over time. Therefore, the intervention preschools will be approached twice while staff participate in the professional development during Year 1 (once at the beginning and once at the end of the period) and once after its completion during Year 2.

Informed by the findings from the qualitative study conducted during the first wave, we will also develop a survey that will be administered during Wave 2 to all members of staff in the intervention preschools. The aim of this survey is to develop theories about how the identified mechanisms in the qualitative findings play out in contexts with different preschools, staff, and children.

##### Evaluation of written plans

As part of the professional development, we will work with and strongly advise all preschools to anchor the child-level core components of the intervention in their written policies and plans. This work will extend the assessment of existing policies and practices as well as the customized intervention aims and models developed in Phase 1 of the education module. We will use these plans to assess to what extent the intervention is integrated in the preschools’ policies and daily operation over the short- and long-term.

##### Participation and engagement in professional development

Participation in the professional development courses and lectures, as well as completion of tasks related to the implementation process, for example, making aims, drafting models of how the preschool will work to incorporate the intervention, and experience sharing, will be logged to allow for a thorough evaluation of the intervention implementation.

##### Observation of the movement environment

The preschools’ movement environment quality and educational practice will be assessed using the Movement Environment Rating Scale (MOVERS) (Archer and Siraj, 2017) observational scale. This scale captures the quality of the early learning environment and practice based on the presence or absence of high-quality experiences and practices identified as being influential for children’s later outcomes. The scale is completed by highly trained and reliable raters through a fly-on-the-wall observation of a preschool room, conducted across a full day and is supplemented by a review of documentation and discussion with an educational leader. All rooms will be scored at baseline, whereas the scale will be used to support and evaluate the implementation process in the intervention group at later time points.

The MOVERS consists of four subscales relating to quality of experiences and practices related to children’s physical development, namely: (*1) curriculum, environment and resources for physical development* (4 items); (*2) pedagogy for physical development* (3 items); (*3) supporting physical activity and critical thinking* (3 items); and (*4) parents/carers and staff* (1 item). The score ranges from 1 to 7, where 1 = inadequate, 3 = minimal, 5 = good, and 7 = excellent. These quality rating scores are determined by in-balance judgments of the pattern of presence or absence of quality indicators for each item. The MOVERS has been used and validated outside Norway, and we will consider whether it needs adapting to the Norwegian context during the project period.

##### Staff Physical activity

Staff PA will be assessed using accelerometry, which will be performed simultaneously with the three child measurements. We will use the same procedures as detailed for children above, except using another criterion for non-wear time and other cut points to determine intensity-specific PA. Consecutive periods of ≥ 60 min of zero counts, allowing for 1–2 min of non-zero counts, will be defined as non-wear time, according to previous studies in adults (Troiano et al., 2008; Hansen et al., 2012). Results will be reported for overall PA level (cpm), as well as minutes per day spent sedentary (<100 cpm), in light PA (100–2,019 cpm), in moderate PA (2,020–5,998 cpm), in vigorous PA (≥ 5,999 cpm), and in MVPA (≥ 2,020 cpm), determined using the previously established Troiano cut points (Metzger et al., 2008). Consistent with children’s activity patterns and handling of child data, results will primarily be analyzed using short epochs (1 s) to allow for capturing short intermittent bursts of PA. Sensitivity analyses using 60-s epochs will be performed as needed for comparison with previous adults studies (Troiano et al., 2008; Hansen et al., 2012).

#### Data Management

High-quality data collection, data management, and data analysis is of crucial importance to ensure valid study results and secure privacy protection of participants. Prior to the data collection, all assessors will perform thorough training in how to instruct and score children on the different measures to ensure high interrater reliability and minimal measurement error.

Non-digital data on main child-level outcomes (anthropometry, physical fitness, motor competence, and self-regulation) will be double-checked for 100% of cases and triple-checked for a random sample of 10% of cases. Other sources of non-digital data will be double-checked using a random sample of 25% of preschools. After the thorough quality control of data, the database will be locked prior to opening the group allocation (1- and 2-years follow-up) and prior to performing any statistical analysis.

Data handling and storage are confidential and will be managed according to the Western Norway University of Applied Sciences internal control system in accordance with Norwegian privacy protection regulations/the General Data Protection Regulation (EU 2016/679).

